### **9.2.3 Safety analysis**

Intervention is non-invasive, potential side effects are only limited to influences upon the skin where the electrodes are placed. Participant discomfort will be closely monitored. Urine test will be conducted before and after the intervention to check for any unintended metabolic changes. Adverse event monitoring will be reported in the full study population and described in a table. Chi-Square test will be used for any comparison of the incidence rate of adverse events between the two groups.

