### 1.2.3 Safety of tES in Children

While there are yet no studies done involving tPCS and children with ASD, the safety of tPCS had been

investigated in childhood cerebral palsy and in adult neurological disorders such as Parkinson's disease, chronic visceral pain and disorder of consciousness, with no adverse events recorded. At present, it is generally considered that an output current between 0-2mA, and the single stimulation time is less than 40 minutes is considered relatively safe. There is no exact guidelines for tES dosing in children although a dose of up to 1mA is typically used. Krishnan C et.al conducted a comprehensive statistical analysis of 48 clinical studies involving more than 513 children and / or adolescents with non-invasive brain stimulation. They found that the most common adverse reaction of tES among people under 18 years of age was skin tingling, with an incidence rate of 11.5%, followed by skin itching, with an incidence rate of 5.8%. These adverse reactions were transient and non-persistent. In terms of cognitive adverse events, treatment-emergent mania and hypomania have been reported in unipolar and bipolar depression treatment in tDCS trials in diseased adults. Finally, drug interactions with tDCS have been reported, with antipsychotics with high D2 affinity such as Haloperidol and Risperidone reported to suppress neuromodulation-induced plasticity while benzodiazepines were associated with an increase in depression scores when used in conjunction with tDCS.

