### **2.4 Potential Risks and Benefits**

#### **2.4.1 Potential Risks**

tPCS may cause discomfort or tingling sensation to some people. Some people may have skin redness due to allergic reaction to electrode. Few people may complain of headache post stimulation. Otherwise, there is minimal risk in tPCS if there are no contraindication.

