### 9.2 Statistical and Analytical Plans

#### 9.2.1 General Considerations

Statistical analysis will be implemented using the IBM SPSS version 27.0. Before applying any statistical test, the data sets will be tested for a normal distribution with the Shapiro–Wilk test. If the data was found to be normally distributed, then one- way analysis of variance ANOVA and Student’s t-test will be used for the comparison between groups. Analysis of Covariance ANCOVA will be used to compare one or more means between groups

while controlling for the effects of one or more covariates (continuous variables that are related to the dependent variable). For comparison with the baseline value, paired t-test or one-way analysis of variance (ANOVA) will be used to compare the differences within the group before and after treatment. If the data was found to be not normally distributed then Kruskal-Wallis test or Mann-Whitney rank-sum test was used for the comparison. In order to correct for multiple comparisons, Bonferroni correction will be used to further validate the significance of each p-value. All statistical tests were conducted using a two-sided test. The  $\alpha$ -value was set to 0.05 for all the statistical tests and < 0.01 for Bonferroni correction. Chi-Squared test was used for categorical data, and Mann-Whitney rank sum test was used for ordinal data.

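### Adverse events are compared between arms only by a chi-square test, with no risk difference or confidence interval, and the Bonferroni rule as worded does not exempt safety

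*Combined protocol and SAP*

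**What the plan says.** Section 9.2.3 commits to a description, "Adverse event monitoring will be reported in the full study population and described in a table", and to one between-arm method: "Chi-Square test will be used for any comparison of the incidence rate of adverse events between the two groups". It also plans urine tests before and after the intervention, but names no comparison of the arms on them. Section 9.2.2 compares the overall dropout rate with the rate of dropout due to adverse events; it does not compare the arms. No section plans a risk difference, a confidence interval, an upper bound, or a power or precision figure for any safety comparison.

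The significance rules are in section 9.2.1, under general considerations. Testing is two-sided throughout. On the level of significance, the text says that it "was set to 0.05 for all the statistical tests and < 0.01 for Bonferroni correction". On multiplicity, it says: "Bonferroni correction will be used to further validate the significance of each p-value". Safety tests are neither included nor excluded by name, and the number of comparisons in the correction is not given.

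**The concern.** A chi-square test answers whether the data are inconsistent with equal rates. It does not say how large an excess the data leave possible, and that is the more useful question about harms. The trial was sized on a standardised efficacy effect, so nothing in the plan ensures that the test can detect a relevant excess.

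The multiplicity rule adds to this. A stricter threshold protects against false claims of benefit. Applied to harms, it works against the child: a real excess must clear a higher bar before it is declared.

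The setting makes this matter. Section 1.2.3 says that tPCS has not yet been studied in children with ASD. Section 9.2.3 starts from the premise that side effects are confined to the skin, although section 2.4.1 also lists headache. A report of no significant difference could easily be taken as reassurance while a sizeable excess remained compatible with the data.

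**Working it through.** **Sizing.** The plan gives no safety power to reproduce. Its efficacy figure is 120 per group for an effect size of 0.36 at 80% power (section 9.1). A two-sample, two-sided 0.05 calculation gives 2 × (1.960 + 0.842)² / 0.36² = 121.1, close to 120. With inflation for dropout, the plan arrives at 340, or 170 per arm (section 4.2).

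**Inputs.**
- n = 170 per arm. Section 9.2.3 reports adverse events in the full study population, and section 4.3 has caregivers fill in the log after each session, so children who leave contribute data until they leave.
- Event rates: itching 5.8% and tingling 11.5%, from the paediatric review cited in section 1.2.3. Using them as sham rates is an assumption. Tingling is also a risk that the protocol names for this device: "tPCS may cause discomfort or tingling sensation to some people".
- Effect: a doubling. This is a scenario chosen for the check; the plan gives none.
- Two-sided alpha of 0.05, and 0.01 if the Bonferroni threshold applies.

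**Formula.** With p0 the sham rate, p1 the active rate and p̄ their mean,

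power = Φ{ [(p1 − p0) − z √(2p̄(1 − p̄)/n)] / √([p0(1 − p0) + p1(1 − p1)]/n) }, and miss rate = 1 − power.

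- Itching, 5.8% to 11.6%, alpha 0.05: (0.058 − 1.960 × 0.03057) / 0.03041 = −0.063; power 0.475; miss rate 52.5%.
- Itching, alpha 0.01: (0.058 − 2.576 × 0.03057) / 0.03041 = −0.682; power 0.248; miss rate 75.2%.
- Tingling, 11.5% to 23%, alpha 0.05: (0.115 − 1.960 × 0.04098) / 0.04050 = 0.856; power 0.804; miss rate 19.6%.
- Tingling, alpha 0.01: (0.115 − 2.576 × 0.04098) / 0.04050 = 0.233; power 0.592; miss rate 40.8%.

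Exact binomial enumeration of the uncorrected chi-square test agrees closely. These are the figures used elsewhere in this point:

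| Sham to active, 170 per arm | Miss rate, alpha 0.05 | Miss rate, alpha 0.01 |
|---|---|---|
| 5.8% to 11.6% | 51.5% | 75.5% |
| 11.5% to 23% | 18.8% | 40.0% |
| 5.75% to 11.5% (tingling rate taken as active) | 51.9% | 75.8% |
| 2.9% to 5.8% (itching rate taken as active) | 74.5% | 91.7% |

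For 80% power, the formula needs 169 per arm (0.05) or 251 (0.01) for the doubling from 11.5%, and 370 or 551 for the doubling from 5.8%.

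**What an interval adds.** Suppose 12/170 active and 6/170 sham children have an event.
- Chi-square: 0.0353² / (0.0529 × 0.9471 × 2/170) = 2.11, p = 0.15.
- Wilson limits: 4.08% to 11.93% (active) and 1.63% to 7.49% (sham). The difference is 3.53 points.
- Newcombe lower limit: 3.53 − √[(7.06 − 4.08)² + (7.49 − 3.53)²] = −1.4 points.
- Newcombe upper limit: 3.53 + √[(11.93 − 7.06)² + (3.53 − 1.63)²] = +8.8 points.

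The p-value is unremarkable, yet an excess of almost 9 points is not excluded. With no event in 170 active children, the exact one-sided 95% upper bound is 1 − 0.05^(1/170) = 1.7%.

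**The case against.** Several counter-arguments have force.

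- **The plan makes no claim that non-significance means safety.** A reader might infer one from a design whose only comparative safety result is a p-value, but no such rule is written. Safety is not an objective or outcome in sections 2.2 and 2.3, and the call for safe treatments in section 1.2 is background, not a trial aim. This stands. The point is about what the planned analysis can show.
- **Bonferroni may not be meant for safety.** Section 9.2.1 introduces it after the tests on scores, and section 9.2.3 does not mention it. Since 0.05/5 = 0.01, the threshold would fit ATEC total plus four subscales, although the plan defines no family. Covering safety is the literal reading, not the only one. The 0.01 column depends on it; the 0.05 column and the missing interval do not.
- **Not every listed effect would usually be missed.** A reader might generalise from itching. At 170 per arm and alpha 0.05, a doubling of tingling from 11.5% is detected about 81% of the time.
- **The 40% dropout allowance does not shrink the safety sample to 102 per arm.** A reader might apply it and obtain higher miss rates. That would require dropouts to supply no adverse-event data, contrary to the full-population reporting and the log after each session.
- **Intervals could be derived later.** If the table gives counts by arm, anyone can compute them, and section 12 promises participant-level data. What is missing is a pre-specified estimate, not the information. This lowers the seriousness but does not remove the gap.

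**Conclusion.** The concern holds in limited form. No interval estimate of excess risk is planned, and the multiplicity wording leaves safety tests exposed to a threshold that serves no purpose for harms. At 170 per arm, the miss rate for a doubling runs from 18.8% (from 11.5%, alpha 0.05) to 75.5% (from 5.8%, alpha 0.01) if the quoted rates are sham rates, and from 51.9% to 91.7% if they are active rates. The assumed sham rate therefore drives the result. The sham device delivers current briefly at the start of each session, so the documents do not settle which case is nearer. The conclusion does not depend on an exact figure: for some plausible excesses, non-significance is about as likely as detection, or likelier, and so would not by itself bound the risk. This is a reporting weakness that is easily corrected, not a design failure.

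**What to change.** In section 9.2.3, make the main safety comparison the risk difference, active minus sham, in the proportion of children with at least one event, with a 95% confidence interval (Newcombe or Miettinen-Nurminen). Give it for any adverse event, for each type, and for withdrawal due to an adverse event. Where no event is seen in an arm, give the exact upper 95% bound. The chi-square p-value can be kept beside the interval. State that safety conclusions rest on the upper confidence limit and that a non-significant test will not be reported as absence of harm.

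In section 9.2.1, state that the Bonferroni correction does not apply to safety comparisons.

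The cost is a few sentences and a few table columns, with no new data and no change of design. There are two downsides. The safety statement will be less favourable, because at 170 per arm with equal rates the 95% interval extends about 5.0 points (at 5.8%) or 6.8 points (at 11.5%) either side. And several unadjusted intervals by event type may show some chance signals, which the report should acknowledge.

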## **10 Direct Access to Source Data/ Documents**

The Principal Investigator and Co-Investigators will permit study-related monitoring, audits and/or IRB review and regulatory inspection(s), providing direct access to source data/document.

## **11 Ethical Considerations**

This study will be conducted in accordance with the ethical principles that have their origin in the Declaration of Helsinki (2013 edition) and that are consistent with the applicable regulatory requirements of Good Clinical Practice in China. This final Clinical Trial Protocol, including the final version of the Participant Information Sheet and Consent Form, must be approved in writing by the Centralized Research Ethics Committee of the lead center, Nanhai Maternity and Children's Hospital, prior to enrolment of any patient into the study. The principal investigator is responsible for informing the Centralized Research Ethics Committee of any amendments to the protocol or other study-related documents, as per local requirement.

### **11.1 Confidentiality of Data and Patient Records**

All data will be entered into a secure password-protected document in the desktop. Identifiable patient data will be anonymized. Access to the full data will only be open to the Principal Investigator and Co-investigators. Collaborators involved in statistical analysis will be given access to anonymized data on a need-to-know basis. Hardcopy of the data forms will be stored in locked cupboards in the respective hospital pediatric departments.

## 12 Publications

Following approval by Research Ethics Committee, the study will be registered on Chinese Clinical Trial Registry ([www.ChiCTR.org.cn](http://www.ChiCTR.org.cn)) by the Principal Investigator. Study results will be published in peer-reviewed scientific literature regardless of the trial's outcome. The CONSORT 2010 Statement will be adhered to in publication of study findings to ensure that international standards of authorship and publication are met. Study results, including participant-level dataset and statistical code will be made available on ResMan database managed by the Chinese Clinical Trial Registry.

## 13 Retention of Trial Document

When the study is completed, the research data will be kept in a secure password-protected document in the desktop at the department. All the documents will be retained for at least 7 years after completion of the research study. The Principal Investigator and Co-Investigators will have access to the data. Regular audits will be done by the Principal Investigator and Co-Investigators to ensure data integrity and accuracy.

## 14 Funding

This study was funded by NUS Department of Psychological Medicine (R-177-000-100-001/R-177-000- 003-001/ R177000702733), National University of Singapore iHeattech Other Operating Expenses (A- 0001415-09-00) and Guangzhou Yirui Charitable Foundation, a charitable organization in China that supports special needs children. The grant amount covers research-related costs such as fees for use of assessment scale and procedure-related costs.

## Appendix 1 – Data Form (ATEC)

### Autism Treatment Evaluation Checklist (ATEC)

This form is intended to measure the effects of treatment.

Name of Child \_\_\_\_\_ ☐ Male Age \_\_\_\_\_  
Last First ☐ Female Date of Birth \_\_\_\_\_  
Form completed by: \_\_\_\_\_ Relationship: \_\_\_\_\_ Today's Date \_\_\_\_\_

*Please circle the letters to indicate how true each phrase is:*

**I. Speech/Language/Communication:** [N] Not true [S] Somewhat true [V] Very true

- |                                                                |                                                        |                                                                  |
|----------------------------------------------------------------|--------------------------------------------------------|------------------------------------------------------------------|
| N S V 1. Knows own name                                        | N S V 6. Can use 3 words at a time
(Want more milk) | N S V 11. Speech tends to be meaningful/
relevant             |
| N S V 2. Responds to 'No' or 'Stop'                            | N S V 7. Knows 10 or more words                        | N S V 12. Often uses several successive
sentences             |
| N S V 3. Can follow some commands                              | N S V 8. Can use sentences with 4 or
more words     | N S V 13. Carries on fairly good
conversation                 |
| N S V 4. Can use one word at a time
(No!, Eat, Water, etc.) | N S V 9. Explains what he/she wants                    | N S V 14. Has normal ability to com-
municate for his/her age |
| N S V 5. Can use 2 words at a time
(Don't want, Go home)    | N S V 10. Asks meaningful questions                    |                                                                  |

**II. Sociability:** [N] Not descriptive [S] Somewhat descriptive [V] Very descriptive

- |                                                               |                                       |                                           |
|---------------------------------------------------------------|---------------------------------------|-------------------------------------------|
| N S V 1. Seems to be in a shell – you
cannot reach him/her | N S V 7. Shows no affection           | N S V 14. Disagreeable/not compliant      |
| N S V 2. Ignores other people                                 | N S V 8. Fails to greet parents       | N S V 15. Temper tantrums                 |
| N S V 3. Pays little or no attention when
addressed        | N S V 9. Avoids contact with others   | N S V 16. Lacks friends/companions        |
| N S V 4. Uncooperative and resistant                          | N S V 10. Does not imitate            | N S V 17. Rarely smiles                   |
| N S V 5. No eye contact                                       | N S V 11. Dislikes being held/cuddled | N S V 18. Insensitive to other's feelings |
| N S V 6. Prefers to be left alone                             | N S V 12. Does not share or show      | N S V 19. Indifferent to being liked      |
|                                                               | N S V 13. Does not wave 'bye bye'     | N S V 20. Indifferent if parent(s) leave  |

**ID. Sensory/Cognitive Awareness:** [NJ] Not descriptive [SJ] Somewhat descriptive [VJ] Very descriptive

- |                                        |                                        |                                          |
|----------------------------------------|----------------------------------------|------------------------------------------|
| N S V, 1. Responds to own name         | N S V 7. Appropriate facial expression | N S V 13. Initiates activities           |
| N S V 2. Responds to praise            | N S V 8. Understands stories on T.V.   | N S V 14. Dresses self                   |
| N S V 3. Looks at people and animals   | N S V 9. Understands explanations      | N S V 15. Curious, interested            |
| N S V 4. Looks at pictures (and T.V.)  | N S V 10. Aware of environment         | N S V 16. Venturesome - explores         |
| N S V 5. Does drawing, coloring, art   | N S V 11. Aware of danger              | N S V 17. "Tuned in" - Not spacey        |
| N S V 6. Plays with toys appropriately | N S V 12. Shows imagination            | N S V 18. Looks where others are looking |

Use this code: [NJ] Not a Problem  
[MI] Minor Problem

[MO] Moderate Problem  
[SJ] Serious Problem

**IV. Health/Physical/Behavior:**

- |                                       |                                      |                                                                 |
|---------------------------------------|--------------------------------------|-----------------------------------------------------------------|
| N MI MO S 1. Bed-wetting              | N MI MO S 9. Hyperactive             | N MI MO S 18. Obsessive speech                                  |
| N MI MO S 2. Wets pants/diapers       | N MI MO S 10. Lethargic              | N MI MO S 19. Rigid routines                                    |
| N MI MO S 3. Soils pants/diapers      | N MI MO S 11. Hits or injures self   | N MI MO S 20. Shouts or screams                                 |
| N MI MO S 4. Diarrhea                 | N MI MO S 12. Hits or injures others | N MI MO S 21. Demands sameness                                  |
| N MI MO S 5. Constipation             | N MI MO S 13. Destructive            | N MI MO S 22. Often agitated                                    |
| N MI MO S 6. Sleep problems           | N MI MO S 14. Sound-sensitive        | N MI MO S 23. Not sensitive to pain                             |
| N MI MO S 7. Eats too much/too little | N MI MO S 15. Anxious/fearful        | N MI MO S 24. "Hooked" or fixated on
certain objects/topics  |
| N MI MO S 8. Extremely limited diet   | N MI MO S 16. Unhappy/crying         | N MI MO S 25. Repetitive movements
(stimming, rocking, etc.) |
|                                       | N MI MO S 17. Seizures               |                                                                 |

## Appendix 2 – Data Form (ABC)

### Autism Behaviour Checklist

Child's Name: \_\_\_\_\_ Gender: \_\_\_\_ Date of Birth: \_\_\_\_\_ Year \_\_\_\_ Month \_\_\_\_ Day

Relationship to the Child: \_\_\_\_\_ Contact Information: \_\_\_\_\_

Date of Form Completion: \_\_\_\_\_ Year \_\_\_\_ Month \_\_\_\_ Day

(Note: The person filling out the form should be the child's parents or someone who has lived with the child for more than two weeks.)

This form lists 57 items related to the child's sensory, behavioral, emotional, and language abnormalities. This form lists 57 items related to the child's sensory, behavioral, emotional, and language abnormalities. Circle the number for those items most accurately describing the child. Do not miss any items.

Note: Sensory Ability (S), Relating Ability (R), Body & Object Use (B), Language Ability (L), and Social & Self-Help Ability (S)

| Item                                                                                                         | Score |   |   |   |   |
|--------------------------------------------------------------------------------------------------------------|-------|---|---|---|---|
|                                                                                                              | S     | R | B | L | S |
| Whirls self for long periods of time                                                                         |       |   | 4 |   |   |
| Learns a simple task but "forgets" quickly                                                                   |       |   |   |   | 2 |
| Frequently does not attend to social/environmental cues                                                      |       | 4 |   |   |   |
| Does not follow simple commands (sit down, come here, stand up) given once                                   |       |   |   | 1 |   |
| Does not use toys appropriately (spins wheels, etc.)                                                         |       |   | 2 |   |   |
| Poor use of visual discrimination when learning (fixates on parts of objects such as size, colour, position) | 2     |   |   |   |   |
| Lacks a social smile (may smile out of context)                                                              |       | 2 |   |   |   |
| Exhibits pronoun reversal (For example, saying 'I' instead of 'you,' etc.)                                   |       |   |   | 3 |   |
| Insists on keeping certain objects with him/herself                                                          |       |   | 3 |   |   |
| . Seems not to hear (despite normal hearing tests                                                            | 3     |   |   |   |   |
| . Speech is atonal and arrhythmic                                                                            |       |   |   | 4 |   |
| 12. Rocks self for long periods of time                                                                      |       |   | 4 |   |   |
| 13. Does not (or did not as a baby) reach out when reached for                                               |       | 2 |   |   |   |
| 14. Strong reactions to minor changes in routine / environment                                               |       |   |   |   | 3 |
| . Does not respond to own name when called out among two or more other names                                 |       |   |   | 2 |   |
| . Lunges and darts about, interrupted by spinning, toe walking, hand flapping                                |       |   | 4 |   |   |
| 17. Not responsive to other people's facial expressions or feeling                                           |       | 3 |   |   |   |

|                                                                                                                                                                                                                                                                                                  |              |   |   |   |   |
|--------------------------------------------------------------------------------------------------------------------------------------------------------------------------------------------------------------------------------------------------------------------------------------------------|--------------|---|---|---|---|
| 18. Seldom uses “yes” or “I”                                                                                                                                                                                                                                                                     |              |   |   | 2 |   |
| Has special abilities in one area -seems to rule out mental retardation                                                                                                                                                                                                                          |              |   |   |   | 4 |
| Does not follow simple prepositional commands (e.g., “put the ball in the box”)                                                                                                                                                                                                                  |              |   |   | 1 |   |
| 21. Sometimes shows no “Startle response” to a loud noise                                                                                                                                                                                                                                        | 3            |   |   |   |   |
| 22. Flaps hands (or other self-stimulating behaviour)                                                                                                                                                                                                                                            |              |   | 4 |   |   |
| 23. Severe temper tantrums and/or frequent minor tantrums                                                                                                                                                                                                                                        |              |   |   |   | 3 |
| 24. Actively avoids eye contact                                                                                                                                                                                                                                                                  |              | 4 |   |   |   |
| 25. Resists being touched or held                                                                                                                                                                                                                                                                |              | 4 |   |   |   |
| Sometimes, painful stimuli (cuts, injections, bruises) evoke no reaction                                                                                                                                                                                                                         | 3            |   |   |   |   |
| 27. Is (or was as a baby) stiff and hard to hold                                                                                                                                                                                                                                                 |              | 3 |   |   |   |
| Item                                                                                                                                                                                                                                                                                      | Score |   |   |   |   |
|                                                                                                                                                                                                                                                                                                  | S            | R | B | L | S |
| 28. Is flaccid(doesn’t cling) when held in arms                                                                                                                                                                                                                                                  |              | 2 |   |   |   |
| 29. Gets desired objects by gesturing                                                                                                                                                                                                                                                            |              |   |   | 2 |   |
| 30. Walks on toes                                                                                                                                                                                                                                                                                |              |   | 2 |   |   |
| 31. Hurts others by biting, hitting, kicking....                                                                                                                                                                                                                                                 |              |   |   |   | 2 |
| 32. Repeats phrases over and over again                                                                                                                                                                                                                                                          |              |   |   | 3 |   |
| 33. Does not imitate other children at play                                                                                                                                                                                                                                                      |              | 3 |   |   |   |
| 34. Often will not blink when a bright light is directed towards eyes                                                                                                                                                                                                                            | 1            |   |   |   |   |
| 35. Hurts self by biting hand, banging head...                                                                                                                                                                                                                                                   |              |   | 2 |   |   |
| 36. Does not wait for needs to be met (wants things immediately)                                                                                                                                                                                                                                 |              |   |   |   | 2 |
| 37. Cannot point to more than five named objects                                                                                                                                                                                                                                                 |              |   |   | 1 |   |
| 38. Has not developed any friendships                                                                                                                                                                                                                                                            |              | 4 |   |   |   |
| 39. Covers ears at many sounds                                                                                                                                                                                                                                                                   | 4            |   |   |   |   |
| 40. Twirls, spins, and bangs objects a lot                                                                                                                                                                                                                                                       |              |   | 4 |   |   |
| 41. Difficulties with toilet training                                                                                                                                                                                                                                                            |              |   |   |   | 1 |
| 42. Uses 5 or less words per day spontaneously to communicate wants or needs                                                                                                                                                                                                                     |              |   |   | 2 |   |
| 43. Often frightened or very anxious                                                                                                                                                                                                                                                             |              | 3 |   |   |   |
| 44. Squints, frowns, or covers eyes when in the presence of natural light                                                                                                                                                                                                                        | 3            |   |   |   |   |
| 45. Does not dress self without frequent help                                                                                                                                                                                                                                                    |              |   |   |   | 1 |
| 46. Repeats sounds or word over and over again                                                                                                                                                                                                                                                   |              |   |   | 3 |   |
| 47. “Looks through” people                                                                                                                                                                                                                                                                       |              | 4 |   |   |   |
| 48. Echoes questions or statements made by other people                                                                                                                                                                                                                                          |              |   |   | 4 |   |
| Frequently unaware of surroundings and may be oblivious to dangerous situations                                                                                                                                                                                                                  |              |   |   |   | 2 |
| 50. Prefers to manipulate and be occupied with inanimate objects                                                                                                                                                                                                                                 |              |   |   |   | 4 |
| 51. Will feel, smell, or taste objects in the environment                                                                                                                                                                                                                                        |              |   | 3 |   |   |
